# Efficacy of Ronopterin (VAS203) in Patients with Moderate and Severe Traumatic Brain Injury (NOSTRA phase III trial): study protocol of a confirmatory, placebo-controlled, randomised, double blind, multi-centre study

**DOI:** 10.1186/s13063-019-3965-4

**Published:** 2020-01-14

**Keywords:** Traumatic brain injury, Outcome, Nitric oxide synthase inhibition, Randomised controlled trials

## Abstract

**Background:**

Traumatic brain injury is a leading cause of death and disability worldwide. The nitric oxide synthase inhibitor Ronopterin was shown to improve clinical outcome by enhancing neuroprotection in a phase IIa trial.

**Methods/design:**

The NOSTRA phase III trial (Ronopterin in traumatic brain injury) is a multi-centre, prospective, randomised, double-blinded, placebo-controlled, phase III trial in Europe. It aims at determining whether the administration of Ronopterin compared to placebo improves neurological outcome in patients with moderate or severe traumatic brain injury at 6 months after injury. The trial is designed to recruit patients between 18 and 60 years of age with moderate or severe traumatic brain injury (Glasgow Coma Scale score ≥ 3) and requiring insertion of an intracranial pressure probe. Trial patients will receive a 48-h intravenous infusion of either Ronopterin or placebo starting at the earliest 6 h and at the latest 18 h after injury. The primary outcome will be the extended Glasgow Outcome Score (eGOS) at 6 months. Secondary outcomes will include the Quality of Life Index (QOLIBRI) at 6 months after the injury and the eGOS at 3 months after the injury. Additionally, effects on mortality, intracranial pressure and cerebral perfusion pressure are evaluated.

**Discussion:**

The trial aims to provide evidence on the efficacy and safety of Ronopterin in patients with traumatic brain injury.

**Trial registration:**

EudraCT, 2013–003368-29. Registered on 9 March 2016.

ClinicalTrials.gov, NCT02794168. Registered on 8 June 2016.

Protocol version 14.0 from 05 November 2018.

## Background

Traumatic brain injury (TBI) is a major cause of mortality and long-term disability, with enormous impact on patients and their families [1]. In Europe an overall incidence rate of 262 per 100,000 for patients admitted with TBI was reported in a meta-analysis [2]. The TBI related costs are high and account for €33 billion in Europe in 2010. The high costs are owed mostly to lifetime productivity losses, particularly when young people are affected [3].

Clinical trials in TBI with pharmacological interventions have failed so far, most likely due to the heterogeneity of the disease and its treatment [4]. The pathophysiology of TBI is complex and involves a variety of processes including - among others - neuroinflammation, brain oedema formation and excitotoxicity. Nitric oxide has been discussed as key player in the development of secondary injury after TBI [5]. Inhibitors of nitric oxide synthase have been tested in animal models of TBI [6]. Due to their unique properties, co-factor analogues such as 4-amino-tetrahydrobiopterin (Ronopterin, VAS203), the anti-pterins, have been found to be particularly useful in animal models of TBI [7, 8].

The safety and pharmacodynamics of Ronopterin were assessed in TBI in an exploratory randomised, placebo-controlled and blinded phase II study (“NO synthase inhibition in traumatic brain injury” (NOSTRA)). In an exploratory analysis the study showed promising results by significantly improving clinical outcome despite the small number of patients enrolled [9]. Ronopterin was found to be safe in general; however, renal failure was observed in the highest-dose group, and this was possibly related to Ronopterin. The mechanism of Ronopterin in kidney function was investigated in healthy volunteers, showing a reversible pharmacodynamic inhibitory effect of Ronopterin on renal plasma flow [10].

The ongoing NOSTRA phase III study is a European multi-centre, blinded, randomised, parallel group, placebo-controlled, phase III trial of Ronopterin administration in adults (age 18–60 years) with acute TBI of moderate or greater severity. Based on the results of the NOSTRA phase II study, the trial is designed to detect clinically relevant differences in clinical outcome (extended Glasgow Outcome Score (Egos) at 6 months after injury) [11] as the primary endpoint.

## Methods/design

### Trial design

NOSTRA-III is a multi-centre, prospective, parallel-group (two groups), blinded, placebo-controlled, randomised, phase III trial of Ronopterin administration to adults with TBI of moderate or greater severity requiring intensive care. The primary objective of this trial is to demonstrate that the eGOS 6 months after injury is improved following administration of Ronopterin compared to a placebo control. Exploratory secondary and adjusted multivariable analyses will also be conducted.

### Trial population and eligibility

A total of 220 evaluable patients with moderate or severe TBI will be enrolled in 31 centres with experience in TBI in France, UK, Spain, Austria, and Germany (Appendix 1). The inclusion and exclusion criteria have been chosen to exclude patients with terminal injuries and patients at risk of renal dysfunction.

Patients can be enrolled to the trial if all of the following criteria apply:
Written informed consent from the patient’s legal guardian or legal representative or deferred consent procedure, according to local requirementsAge 18–60 years, inclusiveExpected to survive more than 24 h after admissionTBI within the last 18 h (infusion must not start earlier than 6 h after the injury)TBI with Glasgow Coma Score ≥ 3 requiring intracranial pressure (ICP) monitoringCatheter placement (intraventricular or intraparenchymal only) for monitoring and management of increased ICPSystolic blood pressure ≥ 100 mmHgWomen of child-bearing potential must have a negative pregnancy test

Patients are excluded if any of the following criteria apply:
Penetrating head injury (e.g. missile, stab wound)Concurrent, but not pre-existing, spinal cord injuryBilateral fixed and dilated pupil (> 4 mm)Cardiopulmonary resuscitation performed post injury, or extracranial injuries causing continuing bleeding likely to require multiple transfusions (> 4 units of red blood cells)Coma due to an exclusive epidural haematoma (lucid interval and absence of structural brain damage on computer tomography (CT))Coma suspected to be primarily due to causes other than head injury (e.g. drug overdose intoxication, drowning/near drowning)Known or CT evidence of pre-existing major cerebral damagePatients who cannot be monitored on their recovery (using the eGOS and QOLIBRI)Patients and relatives of patients who do not understand/speak Spanish, English, French, or GermanDecompressive craniectomy planned prior to randomisationPatients with polytrauma and non-head Injury Severity Score > 18Rhabdomyolysis with serum creatine kinase (CK) > 5000 IU/LInjuries to the ascending aorta and/or carotid arteries and vertebral arteriesSerum creatinine > 1.2 mg/dL (106 μmol/L) in women or > 1.5 mg/dL (133 μmol/L) in menEstimated glomerular filtration rate (eGFR) < 60 mL/minBody mass index (BMI) < 18.5 kg/m^2^ and > 40 kg/m^2^, body weight (b.w.) > 110 kgAny severe concomitant condition (cancer; hematologic, renal, hepatic; coronary disease; major psychiatric disorder; chronic alcohol or drug abuse) that can be ascertained at admissionKnown to have received an experimental drug within 4 weeks prior to current injury

The exclusion criteria are designed to exclude patients with previous kidney damage and patients who cannot be followed up for 6 months.

### Management of traumatic brain injury

The study centres will treat patients according to standard care; however, the centres are requested to follow standardised TBI clinical practice according to current guidelines [12].

### Randomisation

Patients in the trial treatment are allocated to treatment with Ronopterin or placebo in a ratio of 1:1, via a confidential interactive web response system and block randomisation. Balance in treatment allocation across the study participants is enhanced through stratification by both research site (defined by each participating hospital) and by the age of the patient included (two age groups, 18–39 and 40–60 years).

Patients aged 18–39 years represent the group of patients with generally better recovery perspectives than the group of patients aged 40–60 years. The upper age limit was set to 60 years for safety reasons, as in the NOSTRA phase II trial in particular, elderly patients exhibited renal dysfunction [9].

### Trial interventions

The intervention is the intravenous administration of Ronopterin compared to a placebo (0.9% saline) via central venous catheter. A total dose of 17 mg/kg b.w. of Ronopterin is infused over 48 h (daily dose 8.5 mg/kg b.w.). The study drug or placebo is administered over 48 h at the earliest 6 h after injury and at the latest 18 h after the injury.

In the case that serum creatinine values increase by more than 50% from the preceding measurement, the infusion has to be stopped. Any other renal safety parameters that indicate renal deterioration may also cause the infusion to be stopped.

The administration period is followed by a clinical follow-up period of 14 days. Patients are closely monitored in the first three days after the end of the infusion. The clinical period is followed by a post-clinical period with visits at 3 and 6 months (Fig. 1).

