These conservative assumptions on the odds ratio are not unreasonably low, because the treatment effect may be diluted by premature infusion terminations and by missing eGOS values on follow up; such protocol violators are included in the FAS but excluded from the per-protocol set. Under favourable conditions the study has a good chance to demonstrate statistical significance even at the lower alpha level of 0.01 and thus to deliver strong statistical evidence of efficacy.

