### Data monitoring and interim analyses

An independent Data and Safety Monitoring Committee (DMC) monitors the quality of the trial and has access to trial outcome and accumulated safety data, including serious adverse events (SAEs), suspected unexpected serious adverse reactions and mortality. In addition, the DMC will review the safety data from a clinical and safety point of view on an on-going basis (Appendix 4).

Three safety interim analyses will be scheduled: when 40, 80 and 110 patients, respectively, have completed their 14-day clinical observation phase. When 110 evaluable patients in the FAS have received their final assessment of clinical outcome (6-month eGOS), an unblinded interim analysis will be conducted by an unblinded statistician and reviewed by the DMC based on clean data on the primary and secondary target variables and on the latest status of safety data. The outcome of this interim analysis will result in one of three possible recommendations of the DMC to the Sponsor to do one of the following:

Stop the study because of futilityContinue and finalize the study as plannedContinue the study as planned but increase the sample size to a specified number of patients

There is no intention to stop the study in the interim if the data already show significant outcome differences between Ronopterin and placebo. An increase in sample size will be recommended by the DMC guided by conditional power of 90%, based on the current estimate of the treatment effect. The maximum sample size to be considered is 330 patients.

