### Safety and adverse event analyses

Safety analyses will be based on the safety set and will comprise standard descriptive methods. Results of all safety measurements will be summarized by treatment and by pre-treatment period, treatment period, clinical follow-up period (days 3–14) and post clinical follow-up period (3 and 6 months) and across periods overall except for the pre-treatment period.

Descriptive statistics will be calculated for laboratory measurements, vital signs including body weight and body temperature, QT interval, P_t_iO_2_ and renal safety monitoring. Changes from baseline will be summarized using standard statistical characteristics and shift tables. Frequencies of normal, clinically significant abnormal and not clinically significant abnormal findings will be presented overall and for each observation period as indicated above.

The total number of treatment-emergent adverse events (TEAE) and the total number of patients with TEAEs, the total number of TEAEs related to the study drug (certain, probable, possible), the total number of patients with TEAEs related to the study drug, the total number of TEAEs and the total number of patients with serious TEAEs, the total number of patients with TEAEs leading to discontinuation of study treatment and the total number of patients with TEAEs leading to death will be summarized by treatment arm. In addition, adverse event severity, relationship to the study drug, actions taken and other action taken will be summarized.

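### The one mandatory creatinine stop compares each value only with the one before it, so with two or more samples during the infusion a stepwise rise past 1.5 times baseline obliges no stop

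*Protocol article*

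**What the plan says.** Under Trial interventions the protocol article gives one mandatory creatinine rule for the infusion: "In the case that serum creatinine values increase by more than 50% from the preceding measurement, the infusion has to be stopped". The sentence after it adds a permissive provision: "Any other renal safety parameters that indicate renal deterioration may also cause the infusion to be stopped". That provision has no threshold and refers to parameters other than the one just named.

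No other in-infusion creatinine limit appears in the article. The creatinine and eGFR limits under Trial population and eligibility are entry exclusions. Safety and adverse event analyses describes reporting after the fact: "Changes from baseline will be summarized using standard statistical characteristics and shift tables".

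The kidney is the organ at risk that the article itself names. The Background reports from phase II that "renal failure was observed in the highest-dose group, and this was possibly related to Ronopterin". Under Randomisation, "The upper age limit was set to 60 years for safety reasons", with renal dysfunction in elderly phase II patients given as the reason. The Conclusions set the aim of minimising risk, renal risk in particular.

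**The concern.** A rule that refers only to the preceding value detects abrupt jumps. It does not limit the total rise, because each new sample resets the reference. A single step to 1.51 times baseline must stop the infusion, while a larger total rise reached in two steps need not.

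The rule also behaves the wrong way round as monitoring intensifies. The more often creatinine is measured, the smaller each step becomes and the further the total can drift without triggering the obligation.

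At stake is whether a patient with a steady rise during the infusion must come off the drug, or comes off only if the local investigator so decides. The trial runs in "31 centres with experience in TBI in France, UK, Spain, Austria, and Germany", so discretion may be exercised differently from site to site. The question concerns patient safety; the primary efficacy comparison does not depend on it.

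**Working it through.** **Inputs from the protocol article (Trial interventions).** The trigger is a rise above 50% over the preceding value. The infusion lasts 48 h and the total dose is 17 mg/kg.

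**Assumed.** The number n of samples strictly inside the infusion. A sample at 48 h cannot stop an infusion that has ended. The article's text gives no schedule and the figures are not shown, so a range is used. The 50% margin is a design choice, so there is no derived figure to reproduce first.

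**Ceiling without a mandatory stop.** If every step is at most +50%, the highest ratio to baseline after n samples is 1.5^n. The equal step that just reaches 1.5 times baseline is 1.5^(1/n) − 1.

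| Samples inside the infusion (n) | Ceiling 1.5^n | Equal step reaching 1.5 × baseline |
|---|---|---|
| 1 | 1.5 | 50.0% |
| 2 | 2.25 | 22.5% |
| 3 | 3.375 | 14.5% |
| 4 | 5.06 | 10.7% |

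With n = 1 the preceding value is the baseline, so a moving and a fixed reference give the same rule. From n = 2 onward, any equal step above the last column and up to 50% passes 1.5 times baseline with no stop obliged.

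**Which schedules give n of 2 or more.**
- Draws tied exactly to the start of infusion, at 0, 24 and 48 h: one value inside, no gap.
- Once-daily draws at a fixed clock time: if the first falls d hours after the start, with d between 0 and 24, the second falls at d + 24, which is below 48. Two values lie inside unless the start coincides exactly with a draw.
- Twelve-hourly draws at 12, 24 and 36 h: three values inside.

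**Worked example.** Start at 14:00 with draws at 06:00, so samples fall at 16 h and 40 h. Suppose creatinine is 1.00 mg/dL before infusion, then 1.45, then 2.10.
- Step 1: 1.45/1.00 = +45%. No stop obliged.
- Step 2: 2.10/1.45 = 1.448, or +45%. No stop obliged.
- Total: 2.10 times baseline.

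A more modest course of 1.00, 1.25 and 1.55 mg/dL has steps of +25% and +24% and ends at 1.55 times baseline, again with no stop obliged.

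**What a baseline reference would change.** With a second limit at 1.5 times the pre-infusion value, the first example obliges a stop at 40 h. At a constant rate of 17/48 = 0.354 mg/kg per hour, the remaining 8 h amount to 8 × 0.354 = 2.8 mg/kg not given. If the same values came at 12 and 24 h, the stop would come at 24 h and spare 24 × 0.354 = 8.5 mg/kg. The highest value compatible with no mandatory stop would then be 1.5 times baseline for any n.

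**The case against.** **The article condenses a fuller protocol.** Version 14.0 is not shown, and detailed stopping criteria and sampling times commonly stand there. This holds in part: the full protocol may contain a limit tied to baseline or an absolute value, and the fix is conditional on that. It does not remove the point, because the article states a specific mandatory rule and fixes its reference.

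**The schedule is unseen.** The treatment is organised by day, with a daily dose and one vial per day, so infusion-tied draws at 0, 24 and 48 h are plausible and would leave no gap. This stands. The documents do not establish that two or more samples are taken.

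**Gradual deterioration is not ignored.** The discretionary sentence covers other renal parameters. If eGFR is calculated from creatinine (the method is not stated), a doubling of creatinine would show there. These are intensive-care patients, and "the DMC will review the safety data from a clinical and safety point of view on an on-going basis". This also stands, but a discretionary sentence obliges nothing, and committee review of safety data is not a stopping rule for one patient's running infusion.

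**The clinical weight may be small.** The Background also reports that the effect on renal plasma flow in healthy volunteers was reversible, and Trial status reports two interim safety analyses after which the committee approved continuing unaltered. Both temper the urgency.

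A reader might infer that patients are expected to reach 2.25 or 3.4 times baseline on treatment, or that the infusion would continue regardless. The documents support neither. The multiples require close to the maximum permitted rise at every step, and the investigator may stop at any point when other renal parameters indicate deterioration.

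**Conclusion.** The point holds in a limited form. As stated in the article, the sole mandatory creatinine stop has a moving reference, so with two or more in-infusion samples a stepwise rise beyond 1.5 times baseline leaves the stop to discretion. The ceilings are 2.25 times baseline with two samples and about 3.4 times with three.

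The conclusion rests on two things that the article cannot settle: that at least two samples fall inside the infusion, and that version 14.0 has no fixed-reference limit. If either fails, the gap disappears.

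Timing limits the benefit further. Trial status puts the end of recruitment at the end of 2019, and the article was published on 14 January 2020. The change would mainly serve patients added if the interim analysis raises the sample size, to at most 330, or a further pivotal trial of the kind the Conclusions mention. This is a sensible low-cost safety improvement to consider, not a fault that undermines the trial.

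**What to change.** First check whether version 14.0 already has a creatinine limit with a fixed reference. If it does, no change to the rule is needed. If it does not, reword along these lines: the infusion must be stopped if serum creatinine is more than 50% above the previous value, or more than 50% above the last value obtained before the infusion began.

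This applies the trial's own margin to a fixed reference. Keeping the comparison with the previous value still catches a jump that follows an initial fall. A summary by arm of peak creatinine relative to baseline would be a useful optional addition to the shift tables already planned.

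**Cost.** One clause and no new measurement, since creatinine is already needed to check eligibility. It is nevertheless a protocol amendment across 31 centres in five countries. It may lead to a few more stopped infusions, and the article already recognises that "the treatment effect may be diluted by premature infusion terminations"; any added dilution should be slight.

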**Fig. 1 Fig1:**
[figure not shown]
Summary scheme of NOSTRA trial treatment

### Investigational medicinal product

Ronopterin (4-amino-tetrahydrobiopterin, VAS203) is provided as a lyophilizate (1 g/vial). The vials are reconstituted with 50 mL of water at the site by a trained unblinded person, to provide a ready-to-use solution. The final concentration of the drug substance Ronopterin is 20 mg/mL. Two vials are used for each patient (one vial for each treatment day).

The doses for each individual patient are calculated automatically according to the individual body weight, using information from the electronic case report form (eCRF). The calculation results in an individual infusion rate for each patient.

### Treatment masking (blinding)

The trial is conducted as a double-blinded trial. Patients, site investigators, site research coordinators, the Sponsor, central CT scan assessor and the staff in charge of treating the patients will not know the treatment allocation. The infusion solution is prepared by unblinded staff at each centre, who are not involved in the care of trial patients. Depending on the local organisation of the site this can be a pharmacist or a nurse from another ward or from the central pharmacy. The unblinded team passes the ready-to-use Ronopterin solution or placebo (masked in opaque orange syringes), labelled with a random number, patient number and infusion rate, to the blinded team. Emergency unblinding can be done via the interactive web response system or - in the case of problems - by the central pharmacy.

### Data collection

Data on all patients (including excluded patients) will be collected by trained study nurses using a web-based eCRF. Queries are generated automatically or by the clinical research associate. Monitoring is performed by the clinical research organisation and the Sponsor (Appendix 2).

Assessments (eGOS and QOLIBRI) for the 6-month outcome will be performed by the investigators by personal interview at the respective centre or by the investigator visiting the patient. All assessors of the eGOS are trained personally (preferred) or via web-based training.

All data and other information generated will be held in strict confidence. The patients will be identifiable only by their patient number. All documents that identify the patient (e.g. informed consent) are maintained in confidence by the investigator.

The Standard Protocol Items: Recommendation for Interventional Trials (SPIRIT) reporting guidelines are applied [13]. Results of the study will be communicated to participants, healthcare professionals and the public by publication and reporting in clinical trial databases (EudraCT, NCT) without any restrictions.

